### Sample size calculation

Previous audits of Harefield PR Unit have shown that in participants undergoing PR-gym achieve a mean (SD) change in ISW of 58 (67) m. The null hypothesis is that PR-min is inferior to the standard treatment PR-gym. The alternative hypothesis is that PR-min is not inferior to PR-gym. The non-inferiority margin will be defined as half the known MCID using the fixed-margin method with a preserved effect of 50% as recommended by previous guidance, including from the United States Food and Drug Administration.^12 13^ The MCID of the ISW is 47.5 m,^14^ and therefore 24 m will be considered the non-inferiority margin. If there is truly no difference between PR-min and PR-gym, then a minimum of 246 patients (123 in each group) is required to be 80% sure that the lower limit of a one-sided 97.5% CI (or equivalently a 95% two-sided CI) will be above the non-inferiority limit of −24 m. Based on audit data, we anticipate 32% dropout from PR (12% from assessment to starting PR and 20% from starting PR to completing PR). Taking into account dropout, the original minimum sample size required for analysis was 362 patients (181 patients per group). However, owing to the impact of the COVID-19 pandemic on the study (described in the Amendment section), the study sample size was increased by a further 74–436 (218 patients per group).

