### Statistical analysis

For baseline data, continuous and categorical variables will be summarised with descriptive statistics. No significance testing will be carried out. The outcome measures will be described by trial arm and at visits 1, 2 and 3 using descriptive statistics.

The main statistical analyses will estimate the difference in mean primary and secondary outcomes between patients randomised to PR-gym and PR-min by intention to treat principle from visit 1 to visit 2 (8 weeks following visit 1) and visit 1 to visit 3 (12 months following visit 1). Group difference estimates and associated one-sided 97.5% CI will be reported. The group differences will be compared using one-sided two independent sample t-test or non-parametric equivalent. The significance level is set at one-sided significance level of 0.025.

Regarding missing data, the number of baseline variables with complete data will be reported and the primary and secondary outcomes will be analysed as per the recommendations of White *et al*.^15^ Missing postrandomisation assessments will be dealt with using an appropriate method of imputation, depending on the missing mechanism.

Adherence is defined as the number of supervised sessions the participant attends irrespective of the assigned intervention (maximum 16). This will be recorded in both intervention arms. As a dichotomous indicator with eight as the cut-off. The following variables will be recorded in a 3×2 table according to allocated intervention: (1) compliers always receive the allocated treatment; (2) complete defiers do the opposite of the allocated treatment, that is, attend no sessions in allocated treatment; (3) partial defiers are all others not falling in the above groups. Dropout cause will be recorded using the MORECARE classification of reason for attrition.^16^

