In addition to the primary intention-to-treat analysis, the effect of actually receiving treatment as defined in the protocol will also be estimated. If non-compliance rate with PR sessions is >10%, a Complier-Average Causal-Effect (CACE) will be estimated.^17^ The following sensitivity analyses are planned: (1) per protocol; (2) including only those in the upper quartile for baseline ISW; (3) complete case; (4) complier Average Causal Effects (CACE) analysis^17^ and (5) primary diagnosis of COPD; (6) a generalised estimating equation-based analysis to estimate the treatment effects, adjusting for imbalance if the group difference in the percentage of smokers, participants age <70 years, or females is greater than 20% at baseline.

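### Non-inferiority rests on intention to treat alone, although 32% dropout from PR is expected and 74 randomised participants received neither programme; analyses of treated participants have no part in the decision

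*Protocol article*

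**What the plan says.** The Statistical analysis section compares the arms as randomised, by intention to treat, and calls this the primary analysis: "In addition to the primary intention-to-treat analysis, the effect of actually receiving treatment as defined in the protocol will also be estimated". It adds a CACE estimate if non-compliance with sessions exceeds 10%. Then comes a list: "The following sensitivity analyses are planned: (1) per protocol", with complete case and CACE among the later items. No sentence gives per protocol or CACE a role in declaring non-inferiority, or says what is concluded if they disagree with intention to treat. Missing follow-up assessments are to be imputed by a method chosen later, according to the mechanism.

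The Sample size calculation section states "we anticipate 32% dropout from PR (12% from assessment to starting PR and 20% from starting PR to completing PR". The Amendment section reports 74 people who were randomised before the pandemic pause and could receive neither programme. The target was raised from 362 to 436 (218 per group) on their account. The article does not say whether they belong to the intention-to-treat set.

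**The concern.** In a superiority trial, participants who receive neither treatment pull the arms together and work against the claim. In a non-inferiority trial they work for it. PR-min could fall short of PR-gym by the whole margin among people who train, and intention to treat could still pass because a sizeable share of each arm did not train. The plan foresees non-completion on that scale and plans analyses that could show the problem, but it does not let them affect the conclusion. This is a choice the article states, not a detail lost in condensing it.

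**Working it through.** **Inputs from the Sample size calculation and Statistical analysis sections**
- Level: "The significance level is set at one-sided significance level of 0.025".
- Margin: "24 m will be considered the non-inferiority margin". Power is computed on the premise "If there is truly no difference between PR-min and PR-gym".
- SD 67 m, from PR-gym audit participants who "achieve a mean (SD) change in ISW of 58 (67) m".
- Size: "a minimum of 246 patients (123 in each group) is required to be 80% sure"; 181 per arm after dropout, now 218 per arm.
- Dropout from PR 32%, of which 12% never start. From the Amendment section: 74 untreated.
- Not given: how much of the completers' arm difference non-completers show, and whether they attend visit 2. I write r for the share kept and let it run from 0 to 1.

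**1. The plan's own figures reproduce.** n per arm = 2 × 67² × (1.960 + 0.842)² / 24² = 122.4, so 123 per arm and 246 in all. 246 / 0.68 = 361.8, so 362. 362 + 74 = 436.

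**2. Error rate of the intention-to-treat test for the effect in completers.** Set the true difference in completers at −24 m. The intention-to-treat difference is −24c, with c = 0.68 + 0.32r. The chance of declaring non-inferiority is Φ((24 − 24c)/SE − 1.96), where SE = 67 × √(2/n). SE is 7.04 m at n = 181 and 6.42 m at n = 218.

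With r = 0, the intention-to-treat difference is −0.68 × 24 = −16.32 m. At 181 per arm, Φ(7.68/7.04 − 1.96) = Φ(−0.87) = 19.2%. At 218 per arm, Φ(7.68/6.42 − 1.96) = Φ(−0.76) = 22.3%.

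| Assumption about non-completers | c | 181 per arm | 218 per arm |
|---|---|---|---|
| No arm difference (r = 0) | 0.68 | 19.2% | 22.3% |
| Keep half (r = 0.5) | 0.84 | 7.9% | 8.7% |
| Keep three quarters (r = 0.75) | 0.92 | 4.6% | 4.8% |
| Only the 12% never-starters diluted | 0.88 | 6.0% | 6.5% |
| Keep all (r = 1) | 1.00 | 2.5% | 2.5% |

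If non-completers also gain nothing on average, the SD widens to √(67² + 0.68 × 0.32 × 58²) = 72.3 m, and the first row becomes 17.1% and 19.8%.

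**3. The 74.** If they are in the intention-to-treat set with no arm difference, and 32% of the other 362 drop out, c = 246/436 = 0.564. The diluted difference is −13.54 m, and Φ(10.46/6.42 − 1.96) = Φ(−0.33) = 37%.

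**4. Where there is no inflation.** If non-completers have no visit 2 value and are left out, or are imputed to behave like completers of their own arm, c = 1 and the rate is 2.5%. If the target is the effect of being assigned to each programme, the test holds 2.5% by construction.

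**5. Requiring both analyses.** Simulation (200,000 runs per setting; dropout unrelated to outcome; per-protocol set equal to the completers; r = 0) gives a false non-inferiority rate of about 2.3% to 2.5% for the effect in completers. When the arms are truly equal, joint power is about 79% at 362 (123 completers per arm). At 436 it is about 86% with 148 completers per arm (0.68 × 218), or about 79% with 123 per arm if the 74 count as untreated. Per protocol alone has 80% power with 123 per arm, because the plan's 246 is what remains after the 32% are removed.

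**The case against.** The strongest reply is that the protocol's primary contrast is between people as randomised, and for that contrast intention to treat has the stated 2.5%. The Discussion presents the trial as a question about health service delivery, which the effect of assignment can answer. This stands. A reader might infer from the 32% that the plan's false non-inferiority rate is simply well above 2.5%. The documents do not support that, because the inflation exists only for a different target, the effect in people who train.

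Second, the sample size treats the 32% as lost to analysis, whereas the 19% needs them measured or imputed with no arm difference. Twenty of the 32 points are people who start and later stop, and nothing in the article says they show no difference. This also stands, and it is why the result is a range. But the imputation method is left open, so the article does not secure the harmless case either.

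Third, a reader might infer that the plan ignores the effect in treated participants. It does not: per protocol, complete case and CACE are all planned, and the expected non-completion would very probably trigger CACE. These analyses lessen the problem, but they do not enter the decision.

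Fourth, a per-protocol set is selected after randomisation and can be biased in either direction. That argues against replacing intention to treat, not against requiring both. The article also does not equate the eight-session cut-off with completing PR, so the joint power figures are approximate.

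Last, the decision rule could be settled in an analysis plan that is not shown. The article, however, has already fixed which analysis is primary and which are sensitivity analyses.

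**Conclusion.** The concern holds in conditional form. Non-inferiority depends on intention to treat alone, with substantial dilution foreseen and no rule linking it to the analyses of treated participants. For the effect in people who train, with a true deficit of 24 m in completers and an SD of 67 m, the chance of a false claim is about 19% at 181 per arm and 22% at 218 per arm if non-completers show no arm difference. It is about 37% if the 74 are also included. It is about 8% to 9% if non-completers keep half the difference, about 5% at three quarters, and about 6% if only never-starters are diluted. It is 2.5% if non-completers are excluded or imputed like completers of their own arm, or if the target is the effect of assignment. Which of these applies turns on matters the article leaves open: the target effect, how non-completers are measured or imputed, and the status of the 74.

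**What to change.** Before unblinding, state that non-inferiority is declared only if the lower 97.5% limit lies above −24 m in both the intention-to-treat analysis and one named analysis of treated participants: per protocol, using the eight-session cut-off already recorded, or CACE. If the two disagree, non-inferiority is not declared. State also whether the 74 are in the intention-to-treat set. Since the adherence count ignores which programme was assigned, define the per-protocol set by sessions in the allocated programme.

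The rule cannot raise the error rate for either target, since it passes only when both tests pass. It needs no new data and no extra patients. With per protocol, joint power is about one point below the planned 80% at 362, and about 79% to 86% at 436, if dropout is unrelated to outcome and the set is about the 68% who complete. Intention to treat alone, with everyone measured and SD 67 m, would have about 93% at 181 per arm and 96% at 218, so the rule does give up that surplus.

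CACE costs more. If the estimate is the intention-to-treat difference divided by the share treated, the intention-to-treat limit must clear −0.68 × 24 = −16.3 m. Power is then Φ(16.32/7.04 − 1.96) = 64% at 181 per arm and Φ(16.32/6.42 − 1.96) = 72% at 218. It is about 56% at 218 if the 74 are included as untreated. The choice between the two should be made with that in view.

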### Randomisation, allocation and blinding procedures

Consenting participants will be randomised at the individual level with a 1:1 allocation, using an independent web-based system provided by the United Kingdom Clinical Research Collaboration registered King’s Clinical Trials Unit (KCTU), to receive either ‘usual care’ (PR-gym) or intervention (PR-min).

Randomisation by minimisation will ensure that participant characteristics are balanced between the groups with respect to previous completion of PR (yes/no), multiple deprivation index (most deprived quintile of index: yes/no^9^ and frailty status (Short Physical Performance Battery score <10/≥10.^10^ A proportion of patients will be entered initially using simple randomisation in order to create a level of initial imbalance and the minimisation algorithm will maintain a level of randomness in order to preserve prerandomisation allocation concealment. Once randomised, the system will automatically generate a full audit trail of the process and send email to relevant investigators in a blinded or unblinded format, depending on their role. For each arm, participants will be provided with a choice of three sites in northwest London to undertake PR.

Owing to the nature of the interventions, participants and providers of the intervention will not be blinded. However postrehabilitation assessments will be performed by a researcher blinded to group allocation and not involved in the delivery of either intervention arm. The trial statistician will also be blinded to group allocation.

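### The only covariate-adjusted analysis stated in the article depends on a 20% baseline-imbalance trigger that, read as percentage points, will almost never fire; replace it with a prespecified adjusted analysis that always runs

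*Protocol article*

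**What the plan says.** All references are to the Protocol article.

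- **Main analysis (Statistical analysis).** The arms are compared without covariates: "The group differences will be compared using one-sided two independent sample t-test or non-parametric equivalent". The test level is fixed: "The significance level is set at one-sided significance level of 0.025".
- **Sensitivity analysis (6), same section.** This is "a generalised estimating equation-based analysis to estimate the treatment effects", and adjustment is tied to a condition: "adjusting for imbalance if the group difference in the percentage of smokers, participants age <70 years, or females is greater than 20% at baseline". No other analysis in the article is stated to adjust for anything.
- **Baseline data, same section.** Baseline variables are described only: "No significance testing will be carried out".
- **Randomisation, allocation and blinding procedures.** Participants are "randomised at the individual level with a 1:1 allocation". Minimisation keeps the arms "balanced between the groups with respect to previous completion of PR (yes/no), multiple deprivation index", and also on "frailty status (Short Physical Performance Battery score <10/≥10". None of the three trigger variables is a minimisation factor, and no stated model contains a minimisation factor or baseline ISW.

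**The concern.** A reader of the list of sensitivity analyses would expect the primary result to be checked against a covariate-adjusted estimate. Whether that estimate exists depends on the size of an observed baseline difference. In a properly randomised trial, a difference in a variable that was not minimised on arises by chance, and its size says nothing about whether the variable predicts ISW change. A modest gap in a strongly prognostic variable matters more than a 20-point gap in a weak one, yet the rule ignores the first and acts on the second.

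Three further features weaken the rule:

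- The 20% is not labelled as percentage points or as a relative difference, and the two readings behave very differently.
- The variables most naturally adjusted for in this design, baseline ISW and the three minimisation factors, are not in it.
- Age enters only as below 70 or not.

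At stake is a robustness check that the plan appears to contain but would not produce, together with the precision that adjustment could bring to a non-inferiority comparison planned at 80% power.

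**Working it through.** **Inputs (Sample size calculation).** SD of ISW change 67 m; margin 24 m; one-sided 0.025; 80% power; true difference 0; 123 per arm evaluable; 32% dropout; 362 randomised originally (181 per arm); 436 after the amendment (218 per arm). The document gives no prevalence for smoking, age below 70 or female sex, and no R² for any covariate. Those values are assumptions below.

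**1. The plan's own figures reproduce.** n per arm = 2 × 67² × (1.960 + 0.842)² / 24² = 122.3, rounded up to 123, or 246 in total. 246 / 0.68 = 361.8, rounded up to 362. 362 + 74 = 436. The point does not touch the sample size.

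**2. Chance of the trigger, percentage-point reading.** SE of the difference in proportions = √(2p(1−p)/n), largest at p = 0.5.

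- n = 218: √(0.5/218) = 0.0479, so 0.20/0.0479 = 4.18 SE
- n = 123: √(0.5/123) = 0.0638, so 0.20/0.0638 = 3.14 SE

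Exact probabilities that two independent binomial proportions differ by more than 0.20:

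| Per arm | Prevalence | Per variable | Any of three |
|---|---|---|---|
| 218 | 50% | 0.003% | 0.009% |
| 218 | 20% | 0.00002% | 0.00006% |
| 181 | 50% | 0.012% | 0.036% |
| 123 | 50% | 0.17% | 0.52% |

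Prevalences of 10% to 50% were scanned and 50% gives the maximum. The any-of-three column assumes independence, but three times the single-variable figure is an upper bound whatever the correlation and gives the same rounded values. The 123-per-arm row is a deliberately small case, because the rule speaks of baseline, where all randomised participants count.

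**3. Imbalances that do occur.** At 218 per arm and p = 0.5, a gap above 10 points has probability 3.9% per variable (11% for any of three). A gap above 5 points has probability 31% (68%). The trigger leaves all of these unadjusted up to 20 points.

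**4. Relative reading.** If 20% means that the larger arm exceeds 1.2 times the smaller, the rule at 218 per arm fires with probability 5.8% at prevalence 50%, 34% at 20% and 52% at 10%. For any of three, with assumed prevalences of 20%, 50% and 45%, it fires about 43% of the time.

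**5. What adjustment could bring.** Adjustment that explains a share R² of the outcome variance reduces the SD to 67 × √(1−R²). With 123 per arm and margin 24 m:

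| Assumed R² | Power, adjusted |
|---|---|
| 0 | 80.2% |
| 0.05 | 82.2% |
| 0.10 | 84.2% |
| 0.20 | 88.1% |
| 0.30 | 91.9% |

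**6. Direction of error in the unadjusted test.** Suppose the minimisation factors explain R² of the variance, are perfectly balanced, and are left out of the model. The reported SE is then too large, and the actual one-sided error is 1 − Φ(1.960/√(1−R²)): about 0.022 at R² = 0.05, 0.019 at 0.10 and 0.014 at 0.20. The test errs on the conservative side.

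**The case against.** The strongest reply is that this is the last of six sensitivity analyses and that no non-inferiority conclusion depends on it. The primary t-test, margin, level and sample size are unaffected. That stands, and it limits the weight of the point.

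A second reply is that model content belongs in the statistical analysis plan, which is not shown. This stands in part: the statement that no other adjusted analysis exists applies to this article only. The trigger itself, however, is a rule the article states, not a detail it leaves out. The text can also be read as running the generalised estimating equation (GEE) analysis in any case, with only the adjustment conditional. Either way, no adjusted estimate appears unless the trigger fires.

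Two stronger readings are tempting, and the document does not support them:

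- **That the confidence interval would be invalid if the trigger fired.** The rule looks only at allocation and baseline variables, never at the outcome, and its three candidates are named in advance. In simulations at 123 per arm with SD 67 m and an assumed covariate effect of 20 or 40 m, coverage of the 95% interval was about 95%, both with an imbalance of about 20 points imposed and under the adjust-if-triggered rule overall.
- **That the GEE analysis needs data missing completely at random.** That would hold for an unweighted GEE on observed data alone. The article does not say the GEE is unweighted, it plans imputation of missing post-randomisation assessments according to the missingness mechanism, and it lists complete case as a separate sensitivity analysis.

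Nor does the decision not to test baseline differences contradict the trigger. It shows only that the plan avoids one use of baseline imbalance while relying on another.

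**Conclusion.** The point holds as a moderate one that should be changed. On the percentage-point reading, which is the more natural one for a difference in a percentage, the adjusted analysis would be produced in at most about 0.009% of trials at full size and about 0.5% at 123 per arm, whatever the prevalences. On the relative reading it could be produced often, about 43% of the time under the assumed prevalences, and chance would decide. Neither reading gives a dependable adjusted check, and neither brings in baseline ISW or the minimisation factors.

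The probabilities treat allocation as simple randomisation with respect to smoking, age and sex, since none is minimised on. The power gains rest on assumed R² values. The unadjusted primary analysis is valid, and conservative to the extent that the minimisation factors are prognostic. The benefit of the change is therefore precision and robustness; it does not correct any inflation of error.

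**What to change.** Delete the imbalance trigger from sensitivity analysis (6). In its place, state an analysis of the ISW outcome that always runs and is adjusted for baseline ISW and the three minimisation factors (previous rehabilitation, deprivation, frailty status). Add continuous age, sex and smoking if they are judged prognostic before outcome data are seen. If any imbalance threshold is kept for descriptive purposes, say whether it is in percentage points or relative.

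The GEE framework can stay; moving to a mixed model is optional and is not required by this point.

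The cost is a change of wording in the protocol and analysis plan. All the covariates are baseline variables: ISW and the Short Physical Performance Battery are scheduled at visit 1, the minimisation factors are needed at randomisation, and smoking, age and sex are already used by the present rule. The sample size does not change.

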### Data collection, management and monitoring

A web based electronic data capture (EDC) system has been designed using the InferMed Macro 4 system and will be maintained by KCTU for the duration of the project. Source data will be entered by recruiting site staff, typically within 1 week of data collection by authorised staff onto the EDC. A full audit trial of data entry and any subsequent changes to entered data will be automatically date and time stamped, alongside information about the user making the entry/changes within the system.

The primary investigator (WM) will take overall responsibility for the conduct of MISTER. The trial co-ordinator ([name]) will supervise the day-to-day operation of the project and is responsible for ensuring that Good Clinical Practice guidelines are followed. An unblinded member of the MISTER research team ([name]) will monitor the data and review a random sample of 10% of completed case report forms against clinical records. Monitoring will ensure protocol compliance, proper study management and timely completion of study procedures.

